### Substudy analyses

A number of substudies will be performed based on the data acquired during the main study. These will not interfere with the aims and the conduct of the main trial but will provide valuable additional data. The major substudies are:

1. Determination of an ischaemic threshold for revascularisation with semi-quantitative and fully quantitative perfusion analysis.

2. Correlation between the results of FFR and CMR perfusion.

3. Ischaemia reduction in the MR-INFORMED vs the FFR-INFORMED group

4. The effect of new scar formation on outcome.

5. The cost-effectiveness of an MR-INFORMED vs a FFR-INFORMED revascularisation strategy.

### Data collection and monitoring

Patient demographic details, medical history and information on current medication use will be collected. A 12 lead ECG will be performed at baseline and at 12 months. Blood tests will include a measurement of total cholesterol and full lipid profile, a random glucose measurement, and renal function (eGFR). These tests will be repeated at 6 and 12 months. A full blood count will also be measured at baseline. Blood pressure, waist circumference measurement, and Body Mass Index will be determined at baseline, 6 and 12 months.

At the time of revascularisation (PCI or CABG), baseline troponin will be measured. This will then be repeated 6 hours post PCI or 12 hours post CABG. If the troponin is raised, then a CKMB will be done at 12-24 hours post PCI or 36-72 hours post CABG. The definition of myocardial infarction is based on CKMB. See Table 1 for detailed definitions of end-points.

All study data is recorded via an electronic case report form (eCRF). Data will be monitored at all sites for completeness and quality by the contract research organization (CRO). A full data-monitoring schedule will be established and an independent data monitor will verify the eCRF against the source data.

Any adverse events or serious adverse events are recorded on the eCRF and forwarded to the sponsor and the CRO immediately. An independent Data Monitoring Committee will review serious adverse events and any other trial safety issues.

### Organisation

The trial has been approved by the ethics committees either nationally or locally depending on site stipulations in each country. A CRO has been contracted to oversee the monitoring of all sites, establishing the eCRF and checking the completeness and consistency of the trial data.

A trial steering group has been appointed to help the chief investigator with the scientific aspects of the trial and to oversee the progress of the trial. They will also advise on any major protocol modifications suggested by the investigators.

### Statistical considerations

#### Sample size

The sample size calculation is based on the primary endpoint of death, MI, and repeat revascularisation at one year. A 10% event rate in the FFR group and an equivalence margin of 6% were assumed based on the results of the FAME study [5]. A sample size of 826 would be required to determine the non-inferiority of aCMR guided strategy compared to an FFR guided strategy with at least 80% power. Allowing for a dropout rate of 10% a total sample size of 918 patients is necessary. The calculation was carried out using STATA 11SE.

We do anticipate that there will be crossover between groups, most likely from the CMR group to the FFR group, when patients continue to experience symptoms and the CMR scan has been reported as negative. This will be taken into consideration during the statistical analysis which will be done on a per protocol and an intention to treat basis.

### Data analysis

#### Primary analysis

The main objective of this study is to assess whether an “MR-INFORMED” management strategy is non-inferior to an “FFR INFORMED” strategy for the clinical management of patients with angina who are at moderate to high risk of CAD. To satisfy this objective the study will test the following null-hypothesis:

H_0_: The difference in MACE incidence rates between MRI and FFR group is above or equal to δ .

The outcome will be primarily assessed on an intention to treat basis (mITT) and secondarily on a per protocol (PP) analysis. The null hypothesis H_0_ can be rejected and non-inferiority of the MR-guided strategy claimed, if the two-sided 95% confidence interval (CI) for the difference in incidence rates is completely below δ in both the (mITT) and (PP) analysis. A difference of 6%-points was regarded as clinically relevant. Therefore the non-inferiority margin was set to 6%-points.

In addition, absolute and relative frequencies will be given per group. All statistical analyses will be carried out by an independent statistician. A formal interim analysis is not planned in this study.

For all secondary efficacy variables, descriptive statistics (n, mean, standard deviation, median, minimum, and maximum) will be calculated for each quantitative variable. Absolute and relative frequencies will be given for categorical data.

### Cost-utility analysis

The economic analysis will compare the total costs and effectiveness within each arm of the treatment and provide incremental cost effectiveness ratio (ICER). It will be computed as incremental costs divided by increment quality adjusted life years (QALY). The total costs will include both the direct and indirect costs. Costs will be computed by recording patient utilisation of all NHS services for the follow-up period of one year. These include, for instance, the costs of the initial diagnostic procedures (CMR, coronary angiography and FFR), revascularisation (PCI or CABG), hospitalisation costs, pharmacy costs, optimal medical therapy costs over the two years plus costs associated with any re-hospitalisation due cardiac events (MI, repeat revascularisation). These costs will be assessed using the NHS reference costs. Additional costs will be computed using patient diaries and will include direct health care expenditures plus total time off work (to compute lost income), travel time and any travel or work time costs incurred by home care givers (e.g. spouse, parent, etc.). Quality of Life assessment will be carried out using the EQ5D questionnaire and will be administered at base line and every two months for up to 24 months. Bootstrap methods will be used to derive confidence intervals around the ICER and to derive the Cost Effectiveness Acceptability Curve (CEAC).

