### Secondary endpoints

• Symptoms (angina score, NYHA class) within 1 year.

• Death, myocardial infarction and repeat revascularisation as individual components of MACE.

• Cost-effectiveness of a CMR vs FFR guided selection for vascularisation.

• Occurrence of new myocardial scar tissue.

• Ischaemia reduction in the FFR vs CMR group after therapy.

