### Study conduct and randomisation

MR-INFORM is a multi-centre, randomised controlled, non-inferiority trial. It is actively recruiting within the UK, Germany and Portugal. The study is performed in accordance with the principles of the Declaration of Helsinki; with all patients providing informed written consent prior to testing. The study protocol and other relevant documentation have been approved by the South London Ethics Committee (UK) and the relevant national ethics committees as well as registered on ClinicalTrials.gov identifier: NCT01236807: (http://clinicaltrials.gov/ct2/show/NCT01236807?term = MR + INFORM&rank = 1). Suitable patients are identified in the outpatient clinics and from the angiography and CMR waiting lists of the recruiting centres. If they meet the inclusion criteria and none of the exclusion criteria and provide written informed consent, they are enrolled into the study.

Patients are electronically randomised prior to the baseline CMR scan via a web-based randomisation service into randomly varying block sizes of 2 and 4, stratified by study site and gender with an allocation ratio 1:1 to MR-INFORMED or FFR- INFORMED (Figure 1).

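### The unconditional bootstrap confidence interval around the ICER is likely to be uninterpretable if the QALY difference is near zero; a net-benefit interval from the same replicates should carry the uncertainty

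*Protocol article*

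**What the plan says.** Cost-effectiveness is one of five secondary endpoints (Secondary endpoints: "Cost-effectiveness of a CMR vs FFR guided selection for vascularisation"). The Cost-utility analysis section defines the ICER as the cost difference divided by the QALY difference and gives two summaries of uncertainty in one sentence. The first is the interval: "Bootstrap methods will be used to derive confidence intervals around the ICER". The second, for which the sentence goes on to use the same bootstrap, is the acceptability curve (CEAC). The section names no willingness-to-pay threshold, bootstrap variant, expected QALY difference or QALY SD, and gives no rule for replicates that fall in different quadrants of the cost-effectiveness plane.

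On the design, the article says "MR-INFORM is a multi-centre, randomised controlled, non-inferiority trial". The Sample size section says "A 10% event rate in the FFR group and an equivalence margin of 6% were assumed" and gives no separate rate for the CMR arm. Study limitations expects low event rates in both arms. The Summary presents CMR as an attractive non-invasive alternative, not as a strategy with better outcomes.

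**The concern.** An interval for a ratio can be read only if the denominator stays clear of zero. Take differences as CMR minus FFR. Replicates that are cheaper and better, and those that are dearer and worse, both give a negative ICER. Replicates that are cheaper and worse, and those that are dearer and better, both give a positive one. As the QALY difference approaches zero, the ratio goes to plus or minus infinity. Sorting such values does not rank them by value for money, so the 2.5th and 97.5th percentiles are not limits of anything a decision-maker can use.

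A non-inferiority trial is where this is most likely to happen. The published interval could run from a large negative to a large positive figure and look inconclusive, while the acceptability curve from the same replicates shows a high probability that CMR guidance is cost-effective.

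**Working it through.** **1. The plan's own sample size.** Inputs from Sample size and Primary analysis: 10% event rate, margin 6 percentage points, two-sided 95% interval (one-sided 0.025), 80% power, 1:1 allocation. A 10% rate in the CMR arm is my assumption.

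- Unpooled formula: n = (1.96 + 0.8416)² × 2 × 0.10 × 0.90 / 0.06² = 392.4, so 393 per arm, 786 in total.
- Score variance with rates restricted to differ by 0.06 (0.0774 and 0.1374): n = [(1.96 × 0.4359 + 0.8416 × 0.4243) / 0.06]² = 407.6, so 408 per arm, 816 in total.
- Power at 413 per arm: Φ(0.06 / √(0.18/413) − 1.96) = Φ(0.914) = 82.0%.
- Dropout: 826 / 0.9 = 917.8, so 918.

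The stated 826 and 918 therefore fit equal true MACE rates. That supports, but does not state, an expectation of near-equal effectiveness. It says nothing directly about QALYs.

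**2. How often the QALY difference is indistinguishable from zero.** With 413 per arm, SE = SD × √(2/413). The chance that the 95% interval includes zero is Φ(1.96 − d/SE) − Φ(−1.96 − d/SE), where d is the true difference. The QALY SDs and differences are assumptions.

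| QALY SD | SE | 95% half-width | d = 0 | 0.005 | 0.01 | 0.02 | 0.03 |
|---|---|---|---|---|---|---|---|
| 0.1 | 0.0070 | 0.014 | 95% | 89% | 70% | 18% | 1% |
| 0.2 | 0.0139 | 0.027 | 95% | 94% | 89% | 70% | 42% |
| 0.3 | 0.0209 | 0.041 | 95% | 94% | 92% | 84% | 70% |

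For SD 0.1 to 0.2 the range is 70 to 95% at 0 to 0.01, and 1 to 70% at 0.02 to 0.03. Simulation agreed within sampling error (about 69 to 95% and 1 to 72%).

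**3. What the ICER interval then looks like.** Simulated trials used a true saving of 1,000 pounds and cost SDs of 2,000 to 4,000 pounds (assumptions), with costs and QALYs uncorrelated. At a true QALY difference of 0, the median percentile limits were about −0.8 to +0.8 million pounds per QALY (QALY SD 0.2) and −1.6 to +1.6 million (SD 0.1).

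**4. One illustrative trial.** This had a true QALY difference of 0, SD 0.2 and a true saving of 500 pounds. The observed differences were −0.0050 QALY and −639 pounds.

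- 36% of replicates were cheaper and better; 64% were cheaper and worse.
- Percentile ICER limits: about −712,000 to +645,000.
- CEAC from the same replicates at thresholds of 0, 10,000, 20,000 and 30,000: 1.00, 0.996, 0.953 and 0.861.
- Net monetary benefit (threshold × QALY difference − cost difference), 95% interval: 156 to 1,037 at 10,000 and −102 to 1,201 at 20,000.

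The net-benefit figures can be read; the ICER limits cannot.

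**5. Whether the planned CEAC covers the gap.** In the set-up of step 3 with a threshold of 20,000 and a QALY difference of 0, the lower 95% net-benefit limit exceeded zero in 99.9, 89.6, 89.6 and 73.1% of trials across the four SD combinations. The CEAC reached at least 0.975 in the same percentages. The two are the same event: a share of at least 0.975 of replicates with positive net benefit puts the 2.5th percentile of net benefit above zero.

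**The case against.** The strongest reply is that the same sentence already plans the CEAC. A reader might infer from the ICER interval alone that the economic analysis cannot show whether CMR guidance is cost-effective. The documents do not support that: as step 5 shows, a CEAC built from net benefit answers the question as well as a net-benefit interval does. Scoring the ICER interval by whether it falls below a threshold makes the loss look very large, but that rule, the threshold and the percentile method are not in the article. The rule also counts cheaper-and-worse replicates with a large ratio as failures, although they favour CMR. This part of the reply stands in full.

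A second reply is that near-equal QALYs are inferred. Non-inferiority concerns one-year MACE, whereas QALYs from EQ-5D also reflect symptoms and procedure burden, and no cost saving is stated either. This stands too. At a true difference of 0.02 to 0.03 with SD 0.1, the interval includes zero in only 18% down to 1% of trials and the problem largely disappears.

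A third reply is that quadrant handling and thresholds belong in a full economic plan. That is fair for details left unstated, but the ICER interval is stated, without condition. The CEAC does not make that interval readable, and another bootstrap variant would not remove the sign ambiguity.

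**Conclusion.** The point holds in limited form. An interval that the article commits to is likely, not certain, to be uninterpretable. The likelihood rests on an inferred QALY difference near zero, an assumed SD of 0.1 to 0.2 and 413 per arm. The chance that the QALY interval includes zero is about 70 to 95% at a difference of 0 to 0.01, but ranges from about 1 to 70% at 0.02 to 0.03.

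The defect is confined to the ICER interval. The CEAC remains valid if built from net benefit, so the secondary endpoint can still be answered. The primary analysis, sample size and data collection are untouched. Severity is minor; it merits correction because the remedy is nearly free.

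**What to change.** In the Cost-utility analysis section, make the main uncertainty summary a 95% bootstrap confidence interval for incremental net monetary benefit at pre-stated thresholds. Alongside it, report the cost and QALY differences each with a 95% interval, the cost-effectiveness plane, and the CEAC derived from the same net-benefit replicates. Report an interval around the ICER only if the replicates do not cross a zero QALY difference and stay in one quadrant where the ratio has meaning.

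The cost is a change of wording: the data and the bootstrap replicates are the same. The one small downside is that the willingness-to-pay thresholds must be named in advance.

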### Study limitations

In this prospective outcome trial we address an important clinical question. There is currently insufficient evidence on the comparative effectiveness of different diagnostic strategies in patients with stable coronary artery disease and therefore we believe that the results of this trial will help to inform future guidelines.

In order to achieve this objective, the trial has been designed to reflect “real-world“ medical practice as closely as possible. This is important for the translation of its results into routine clinical practice. However, inevitably this leads to some limitations in the study design.

Although we aim at optimising medical therapy in both groups, there are variations on what is deemed optimal in different health systems and the implementation of this is left to the primary care physician. We follow the UK guidelines to minimise variation as much as possible, the remaining variation reflects clinical practice.

A critical point is the inclusion of peri-procedural myocardial infarction and target lesion revascularisation in our end-point. These endpoints are frequently used in interventional trials. The occurrence of peri-procedural myocardial infarctions seems an important end-point as they are associated with adverse outcome and may reflect better guidance by one technique or the other. However, as we guide revascularisation by objective proof of ischaemia in both arms, we expect that all patients in the trial are guided towards fewer revascularisation procedures compared to angiography alone and that this will be reflected in low event rates in both arms. The rationale for using target lesion revascularisation is similar.

It is difficult to predict the frequency of crossover from one arm to another, which can be substantial (e.g. COURAGE trial). We do not anticipate a high rate of cross-over, however, the data monitoring committee will assess the occurrence of cross-over and allow for adaptation of the randomisation scheme to account for this.

### Summary

MR–INFORM is an international, prospective, randomised controlled, non-inferiority outcome trial comparing the role of CMR perfusion to routine coronary angiography with invasive fractional flow measurements for guiding patients with stable angina and an intermediate to high likelihood of coronary artery disease. Non-inferiority of CMR perfusion imaging to the current invasive reference standard (FFR) would establish CMR perfusion imaging as an attractive, non-invasive alternative to current diagnostic pathways. The results will help to inform national and international guidelines on the investigation and management of coronary artery disease, and ultimately lead to improved patient care.

### Trial status

MR-INFORM is currently recruiting in the UK, Germany and Portugal. There are currently six sites active in the UK and one in Portugal and Germany. Another six German sites and three UK sites are currently undergoing ethics approval or contract negotiation and should be initiated soon. The number of patients recruited at the time of submission is 235.

## Abbreviations

AHA: American Heart Association; ACC: American College of Cardiology; ACE: Angiotensin Converting Enzyme inhibitor; AV: Atrio-Ventricular; BMI: Body Mass Index; CAD: Coronary Artery Disease; CABG: Coronary Artery Bypass Graft; CCS: Canadian Class Score; CEAC: Cost Effectiveness Acceptability Curve; CK: Creatinine Phosphokinase; CKMB: Creatinine Phosphokinase MB Isoenzyme; CMR: Cardiovascular Magnetic Resonance; COPD: Chronic Obstructive Pulmonary Disease; CRO: Contract Research Organisation; CTO: Chronic Total Occlusion; CXA: Coronary Xray Angiography; ECG: Electrocardiogram; eCRF: Electronic Case Report Form; eGFR: Estimated Glomerular Filtration Rate; FFR: Fractional Flow Reserve; ICER: Incremental Cost Effectiveness Ratio; ITT: Intention To Treat; LAD: Left anterior descending artery; LBBB: Left Bundle Branch Block; LDL: Low-Density Lipoprotein; RCA: Right Coronary Artery; MI: Myocardial Infarction; MACE: Major Adverse Cardiac Event; NYHA: New York Health Association; OMT: Optimal Medical Therapy; PCI: Percutaneous Coronary Intervention; PP: Per Protocol; QALY: Quality Adjusted Life Years; SA: Short Axis; SSFP: Steady State Free Precession; SPECT: Single-Photon Emission Computed Tomography; ULN: Upper Limit of Normal.
